### **11.1.3 Secondary Outcome Measures**

Analyses of secondary outcomes (i.e. incidence of *P. malariae* or *P. ovale* clinical episodes or time to first *P. malariae* or *P. ovale* infections) will follow the same approaches as those employed for analyses of *P. falciparum* and *P. vivax* infections and morbidity, as described above.

## **11.2 Sample Size Considerations**

### **11.2.1 Primary Outcome Measures**

No estimates for time to first *P. vivax* infection are available for the study community however, in the above-mentioned treatment time-to-reinfection study in children 6-12 years of age in neighbouring Madang province the median time re-infection was 54 and 118 days for PCR and light microscopically detected *P. vivax* infections, respectively. Assuming a 50% decrease in time to first new *P. vivax* infections following LLIN distribution then a sample size of 200 children per arm be sufficient to find a reduction of 30% (hazard ratio 0.70) and 34% (hazard ratio 0.66) of PCR and LM-detectable *P. vivax* infections in the CQ/PQ/CO compared to the CQ/PL/CO group with a power of 90%. This sample size was increase by 25% to account for loss of follow-up and by 5% for children that receive less than 14 days of directly observed primaquine treatment/

In a recently completed cohort study in this region, the incidence of clinical *P. falciparum* malaria in children aged 1-3 years was estimated at 2.6 episodes per child per year (any density). Although no estimates for the incidence of clinical *P. falciparum* malaria in children aged 5-10 years in this region, in a recent treatment time-to-reinfection study in children 6-12 years of age in neighbouring Madang province, the incidence was estimated at 1.7 episodes per child per year (any density). The recent distribution of long-lasting insecticide treated bednet (LLIN) will have reduced this incidence by 60%.

Thus, assuming an incidence of 0.5 episode of *P. falciparum* per child per year (any density in this cohort of similarly aged children, a sample size of 500 children will thus be sufficient to detect 20% decrease in incidence between the two treatment arms with a power of 90%.

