## Protocol Summary

**Title:** Host and parasites factors contributing to risk of *Plasmodium* re-infection and morbidity in elementary school children in Maprik, East Sepik Province

**Population:** 500 children 5-10 years of age, who are residents of malaria-endemic villages near Maprik in the East Sepik Province, Papua New Guinea (PNG).

**Number of Sites:** 1 field site (4-8 elementary schools, Maprik District, PNG), 4 laboratory sites (Goroka & Madang PNG, Melbourne, Barcelona)

**Study Duration:** 9 months

**Subject Duration:** 9 months

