## 4 STUDY DESIGN

In this study 500-600 children aged 5-10 years will be screened, enrolled and randomized to 2 arms of a longitudinal cohort study. The randomized arms will comprise:

- 250-300 children pre-treated with 3 days Chloroquine (CQ), 4 weeks Primaquine (PQ) and 3 days Coartem (CO)
- 250-300 children pre-treated with 3 days Chloroquine (CQ), 4 weeks Placebo (PL) and 3 days Coartem (CO)

At enrolment all eligible children aged 5-10 years in the study area will be screened for Glucose-6-Phosphate Dehydrogenase deficiency (G-6-PD) and the presence of severe anaemia or malnutrition. Children with less than 60% G-6-PD activity, haemoglobin <5g/dl or severe malnutrition (weight-for-age nutritional Z score [WAZ] <60th percentile) will be excluded from the study. All other children will be randomized to the two treatment arms of the study.

Drug treatment will commence at enrolment. All children will receive CQ on days 1-3. Children will also receive either PQ (0.5 mg/kg) or placebo on days 1-5, 8-12, 15-19 and 22-26 (i.e. Monday to Friday for 4 weeks). During the third week of drug treatment all children will receive CO on days 15-17 (according to national treatment guidelines). Children will be actively monitored for side effects including measurement of haemoglobin levels at days 1, 8, 15 and 22.

Following completion of treatment, children will undergo a clinical examination and a 10 mL venous blood sample will be collected on day 29 (i.e. 26 days after their last dose of CQ, 12 days after their last dose of CO and 3 days after their last dose of PQ or PL).

Subsequently, all enrolled children will be followed using 2-weekly active and continuous passive case detection at a local health centre for 8 months (Week 2-32). Active follow-up consists of morbidity surveillance visits to monitor clinical malaria illness not reported to a health facility, as well as blood sampling for the detection of asymptomatic malaria. These visits will include collection of a medical history of the preceding 2 weeks to determine incidence of malarial infections and bed net usage, a physical examination, measurement of axillary temperature. A 250µl finger prick blood sample will be collected every 2 weeks for the first 12 weeks and 4 weekly thereafter, i.e. weeks 2, 4, 6, 8, 10, 12, 16, 20, 24, 28 and 32.

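### The *P. vivax* sample-size calculation states the bednet effect in the wrong direction; once that is corrected, 200 children per arm do not give the stated 90% power, most clearly for light microscopy.

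*Protocol*

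**What the plan says.** Section 11.2.1 starts from a cohort in a neighbouring province, where "the median time re-infection was 54 and 118 days for PCR and light microscopically detected *P. vivax* infections, respectively". It then adjusts for nets: "Assuming a 50% decrease in time to first new *P. vivax* infections following LLIN distribution then a sample size of 200 children per arm". On that basis it calls "a sample size of 200 children per arm be sufficient to find a reduction of 30% (hazard ratio 0.70" for PCR, and 34% (0.66) for LM, with 90% power. No alpha or sidedness is given there.

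Two paragraphs of the same section treat the same net distribution. For *P. falciparum* the second says: "The recent distribution of long-lasting insecticide treated bednet (LLIN) will have reduced this incidence by 60" per cent.

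For losses, section 11.2.1 adds: "This sample size was increase by 25% to account for loss of follow-up and by 5% for children that receive less than 14 days" of observed primaquine. On enrolment, the Protocol Summary gives "500 children 5-10 years of age", and the *P. falciparum* calculation also uses 500. Section 4 says "In this study 500-600 children aged 5-10 years will be screened, enrolled and randomized to 2 arms", that is 250 to 300 per arm, and section 5.1 repeats the 500 to 600 range.

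**The concern.** A shorter time to first infection means more transmission, so the *P. vivax* sentence gives the nets the opposite sign to the *P. falciparum* paragraph that follows it. Power in a log-rank or Cox comparison depends on the number of events, and this assumption moves that number upward.

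Time to first *P. vivax* infection is a primary outcome (section 8.1.1) and is how section 3 addresses the first primary objective, the contribution of liver stages to *P. vivax* infection. If the true event count is lower, a non-significant LM result could be read as coming from a comparison with 90% power when it had clearly less.

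**Working it through.** **Inputs.** Medians 54 days (PCR) and 118 days (LM), 200 per arm, hazard ratios 0.70 and 0.66, 90% power: all section 11.2.1. Follow-up 32 weeks = 224 days: section 8.1.1. Log-rank test and Cox regression: section 11.3.1.3. Assumed, because not stated: exponential times and two-sided 5%.

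**Formulas.** Control-arm rate λ = ln 2 / median. Expected events at 200 per arm = 200 × [(1 − exp(−λ·224)) + (1 − exp(−λ·HR·224))]. Power = Φ(|ln HR|·√events / 2 − 1.96). Events needed for 90% = 4(1.96 + 1.282)² / (ln HR)².

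**Events needed.** HR 0.70: about 330. HR 0.66: about 243.

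**Step 1, the text as written (medians halved to 27 and 59 days).** About 396 PCR and 350 LM events; power 94% and 97%. The stated 90% is exceeded.

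**Step 2, the direction corrected, rate halved (medians doubled to 108 and 236 days).**
- PCR: event probabilities 0.763 and 0.634, so 200 × 1.397 ≈ 279 events. Power = Φ(0.357 × √279 / 2 − 1.96) ≈ 85%.
- LM: event probabilities 0.482 and 0.352, so 200 × 0.834 ≈ 167 events. Power = Φ(0.416 × √167 / 2 − 1.96) ≈ 77%.
- Hazard ratios detectable with 90% power: about 0.68 (PCR) and 0.60 (LM).

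**Step 3, the range of net effects at 200 per arm.**

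| Assumed net effect | Medians, days (PCR / LM) | Events (PCR / LM) | Power (PCR / LM) |
|---|---|---|---|
| Time halved (literal text) | 27 / 59 | 396 / 350 | 94% / 97% |
| None | 54 / 118 | 362 / 262 | 92% / 92% |
| Time 1.5-fold longer | 81 / 177 | 318 / 205 | 89% / 84% |
| Rate halved | 108 / 236 | 279 / 167 | 85% / 77% |

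A simulated log-rank test on the planned finger-prick visits agrees: 93.6% and 97.4% for the first row, 83.9% and 76.2% for the last.

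**Step 4, enrolment.** The protocol's own inflation gives 200 × 1.30 = 260 or 200 × 1.25 × 1.05 = 262.5 per arm, that is 520 to 525 in total. This exceeds the 500 of the Summary and the lower end of the 500 to 600 range.

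**Step 5, power at the enrolled number.** Children lost during follow-up contribute time at risk until they are lost (section 11.1.2.1). With 250 enrolled per arm, 25% lost over the 224 days and a halved rate, about 312 PCR and 184 LM events are expected: power about 88% and 80%.

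**The case against.** The best defence is that the sentence is a slip of wording and that no sum in it is wrong: on the stated inputs, 200 per arm do suffice for 90%. That stands. A reader might infer that the 90% is an arithmetic error in its own right; the text does not support this, because the shortfall appears only after the direction is put right.

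A second defence is that the intended correction is unknown. A 50% change could mean a halved rate or a time longer by half, and alpha is not given. This also stands, and it is why the result is a range. One-sided 5% would lift PCR to 90.9% with a halved rate, but LM only to 85.1%.

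Three further readings go too far:
- *The net adjustment was never applied.* Unadjusted medians do give about 92% for both outcomes, close to the claim, but the protocol does not say how its figure was obtained.
- *Only about 178 children per arm count (250 × 0.75 × 0.95), so power should be quoted for that number.* This discards all time at risk before loss, contrary to section 11.1.2.1. Nor does section 11.2.1 say that children with incomplete primaquine leave the analysis.
- *Enrolling about 562 (200 / (0.75 × 0.95) ≈ 281 per arm) restores 90% power.* It would retain 200 per arm, and 200 per arm is the number that gives 85% and 77% with a halved rate. Nor is the whole plan too small to retain 200: the range up to 600 allows it.

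**Conclusion.** The direction of the net effect is wrong as written, and the stated power for a primary outcome rests on it. In either corrected direction examined, 200 per arm miss 90% for both outcomes: by about 1 to 5 percentage points for PCR and about 6 to 13 for LM. With a halved rate, LM is short by about 76 of the 243 events needed.

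This rests on exponential times, 224 days, two-sided 5% and the size chosen for the net effect. Censoring at the first antimalarial treatment for another malarial infection (section 11.1.2.3) is not included and would lower power further.

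The enrolment point is secondary. It concerns the 500 in the Summary and the lower bound of the range, both of which lie below the protocol's own inflated target of about 520 to 525.

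**What to change.** In section 11.2.1:
1. Restate the net assumption as a reduction in the rate of first *P. vivax* infection and give the resulting longer medians (about 108 days for PCR and 236 for LM if the rate is halved).
2. State alpha and sidedness.
3. Restate power at 200 per arm (about 85% PCR and 77% LM if the rate is halved), or the hazard ratios detectable with 90% power (about 0.68 and 0.60), marked as conditional on the assumed net effect.
4. Compute power for the enrolled number with time at risk counted up to loss (about 88% and 80% at 250 enrolled per arm, 25% loss, halved rate).

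In the Protocol Summary, reconcile the 500 with the inflated target and with the 500 to 600 of sections 4 and 5.1.

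The cost is a change of wording and less favourable stated power. No added enrolment is required, but the text should not claim that enrolment within the present range restores 90% for both outcomes.

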## 11.3 Analysis Plan

### 11.3.1 Primary Outcome Measures

#### 11.3.1.1 Incidence of clinical *P. falciparum* episodes during follow-up

This is a primary objective of the study and will be evaluated by assessing differences in the risk of *P. falciparum* clinical malaria with in both treatment arms.

The analysis strategy for these outcomes is centered on different variations of Poisson regression. The outcome variables are total number of *P. falciparum* episodes (over 32 weeks of follow-up) and incidence of 1st or only episode. Exposure will be defined as the total risk time per child as outlined above. Analyses will be adjusted for possible covariates including infection status at baseline, sex, age, host genetic traits, and nutritional state of child.

The analyses will be done both for episodes defined as axillary temperature  $\geq 37.5^{\circ}\text{C}$  plus any parasitemia or axillary temperature  $\geq 37.5^{\circ}\text{C}$  plus *P. falciparum*  $> 5000/\mu\text{L}$ .

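### The stated 90% power for a 20% fall in clinical P. falciparum incidence does not follow from the protocol's own inputs, which give about 26%

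*Protocol*

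**What the plan says.** Protocol section 11.2.1 begins with 1.7 clinical P. falciparum episodes per child-year, taken from a study of 6-12 year olds in a neighbouring province. It says that recent bednet distribution "will have reduced this incidence by 60" per cent. It then moves to its working value, "assuming an incidence of 0.5 episode of" P. falciparum per child per year, and concludes that "a sample size of 500 children will thus be sufficient to detect 20% decrease in incidence between the two treatment arms", giving the power as 90%.

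The other inputs are elsewhere in the protocol. Section 4 makes the sample size a total: "In this study 500-600 children aged 5-10 years will be screened, enrolled and randomized to 2 arms", that is, 250-300 children in each arm. Section 11.3.1.1 counts "episodes (over 32 weeks of follow-up) and incidence of 1"st or only episodes, and says of this comparison: "This is a primary objective of the study". Sections 11 and 11.3.1.1 specify Poisson regression. No section states alpha or whether the test is one- or two-sided.

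**The concern.** The power of a Poisson rate comparison depends almost entirely on the number of events. At 0.5 episodes per child-year over about 0.6 of a year, 500 children produce some 140 episodes. That is far too few to separate rates that differ by 20%.

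The claim concerns an outcome listed as primary in section 8.1.1. An ethics committee or reader who takes it at face value would believe that a true 20% reduction would be found nine times in ten. On the protocol's inputs it would be missed about three times in four. A non-significant comparison could then be taken, wrongly, to rule out an effect of that size.

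**Working it through.** **Inputs.** Control rate 0.5 per child-year and a 20% decrease (rate ratio 0.80), section 11.2.1. 250 per arm, half of 500, with 300 as the upper planned figure, section 4. Follow-up 32 weeks = 32/52 = 0.615 year, section 11.3.1.1. Alpha two-sided 0.05 is my assumption; a one-sided case is shown.

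**Formula.** With E0 and E1 the expected episodes per arm, SE(log rate ratio) = √(1/E0 + 1/E1), and power = Φ(|ln 0.80|/SE − z), with z = 1.96 (two-sided 0.05) and |ln 0.80| = 0.223.

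**Attempt to reproduce 90%.**
- E0 = 250 × 0.5 × 0.615 = 76.9; E1 = 76.9 × 0.80 = 61.5.
- SE = √(1/76.9 + 1/61.5) = 0.171.
- 0.223/0.171 = 1.305; power = Φ(1.305 − 1.96) = 0.256.

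A simulation of 200,000 trials gave 25.2%. The stated 90% is not reproduced.

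**Variations, 20% decrease, two-sided 0.05 unless stated.**

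| Case | E0 vs E1 | Power |
|---|---|---|
| 250 per arm, 0.5/year, 32 weeks | 76.9 vs 61.5 | 26% |
| Same, one-sided 0.05 (z = 1.645) | 76.9 vs 61.5 | 37% |
| 300 per arm | 92.3 vs 73.8 | 30% |
| 200 evaluable per arm (250/1.25) | 61.5 vs 49.2 | 21% |
| 250 per arm, 0.68/year | 104.6 vs 83.7 | 33% |
| 250 per arm, 0.5/year, full year | 125 vs 100 | 38% |
| 500 per arm, 0.5/year, 32 weeks | 153.8 vs 123.1 | 45% |
| 300 per arm, full year, one-sided 0.10 | 150 vs 120 | 71% |

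The 200-per-arm row borrows the 25% loss allowance that section 11.2.1 gives for P. vivax, and it treats lost children as contributing no time. Under the censoring rule in section 11.1.2.1 they would contribute some, so with losses of that size power lies between 21% and 26%.

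**Overdispersion.** Repeat episodes in the same child would lower power. With an assumed negative binomial dispersion of 0.5 to 2, the base case falls to 23% down to 18%.

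**Sample size that 90% would need.** n per arm = (1.96 + 1.282)² × (1/(0.5 × 0.615) + 1/(0.4 × 0.615))/(ln 0.80)² ≈ 10.51 × 7.3125/0.0498 ≈ 1,540.

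**Effect the planned size can detect.** Solving the same formula for the rate ratio at 0.5/year and 32 weeks:
- 250 per arm: about 0.59 at 80% power (41% reduction), about 0.53 at 90% (47% reduction).
- 200 per arm: about 0.485 at 90% (about 51% reduction).

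**Precision.** With SE 0.171, an observed rate ratio of 0.80 would have a 95% interval of 0.80 ÷ 1.40 to 0.80 × 1.40, about 0.57 to 1.12, since exp(1.96 × 0.171) = 1.40.

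**Base rate.** 1.7 × (1 − 0.60) = 0.68, not 0.5.

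**The case against.** Several points on the other side stand.

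- **Alpha is not stated.** The 26% therefore rests on an assumption. A one-sided 0.05 test gives 37%, which is still far from 90%.
- **The 0.5 is worded as an assumption.** The source rate comes from another province and a somewhat different age band, and choosing a rate below 0.68 is conservative for power. A reader might infer a plain arithmetic error in the base rate. The text supports only that the step from 1.7 and 60% to 0.5 is unexplained.
- **The trial is not uninformative about this outcome.** A reader might infer that any null result would be worthless. With 250 per arm, power is 80% for a 41% reduction and 90% for a 47% reduction, so a null would still count against effects that large. The shortfall concerns the 20% target.
- **The origin of the 90% cannot be established.** Other inputs come near it: 2.6 per year (the 1-3 year olds' rate) over 32 weeks gives about 85%, and 1.7 per year over a full year about 87%. Neither matches the stated inputs, and neither can be shown to be the source.
- **The enrolment target is tied to P. vivax.** The P. vivax calculation starts from 200 per arm, and 200 × 1.25 = 250. That calculation addresses the first primary objective and does not depend on the sentence at issue.
- **The outcome's rank is not uniform.** Sections 8.1.1, 11.1.2.1 and 11.3.1.1 treat clinical P. falciparum incidence as primary, while section 3 places its rates under the assessment of secondary objectives. Low power alone does not require a change of rank.
- **No misreading is planned.** Nothing in the protocol says that non-significance will be taken as absence of effect. The risk comes from the stated power.

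None of this restores the 90%.

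**Conclusion.** The concern holds for the power statement. At 0.5 episodes per child-year, 250 per arm and 32 weeks, power for a 20% reduction is about 26%, an overstatement of some 64 percentage points. It is about 30% with 300 per arm, about 21% with 200 evaluable per arm, and about 33% if 0.68 is used. These figures assume two-sided 0.05 and no overdispersion; except for the 200-per-arm case they also assume no losses. They are therefore on the optimistic side for a two-sided test.

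A reader might go further and conclude that the trial as a whole is underpowered or that the outcome must be made secondary. The documents support neither: the P. vivax time-to-infection calculation is separate, and the clinical outcome can stay where it is with an honest power statement.

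**What to change.** In section 11.2.1, replace the power sentence with one that states alpha and losses, for example: *At two-sided alpha 0.05, 0.5 episodes per child-year and 32 weeks of follow-up, 500 children give about 26% power for a 20% reduction (about 21% if 200 per arm are evaluable); 90% power exists only for a reduction of about 47% (about 51% with 200 per arm).* Add that these figures assume no overdispersion.

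In the same paragraph, either reconcile 0.5 with 1.7 reduced by 60% (0.68) or give the reason for the lower value. State that a non-significant result will not be read as excluding a 20% reduction.

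The cost is a change of wording in one section, and the stated power becomes less favourable. Enrolment, follow-up, the outcome list and the P. vivax calculation do not change.

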### 11.2.2 Secondary Outcome Measures

The analyses for secondary *P. falciparum* infection outcomes and *P. vivax* malaria outcomes are comparable to those described for *P. vivax* infection and *P. falciparum* episodes above. The relative scarcity of *P. malariae* and *P. ovale* infections and morbidity in the proposed study age group means that the study will lack power to find any but large differences between the two arms (hazard ratio < 0.5).

## 11.3 Analysis Plan

### 11.3.1 Primary Outcome Measures

#### 11.3.1.1 Incidence of clinical *P. falciparum* episodes during follow-up

This is a primary objective of the study and will be evaluated by assessing differences in the risk of *P. falciparum* clinical malaria with in both treatment arms.

The analysis strategy for these outcomes is centered on different variations of Poisson regression. The outcome variables are total number of *P. falciparum* episodes (over 32 weeks of follow-up) and incidence of 1st or only episode. Exposure will be defined as the total risk time per child as outlined above. Analyses will be adjusted for possible covariates including infection status at baseline, sex, age, host genetic traits, and nutritional state of child.

The analyses will be done both for episodes defined as axillary temperature  $\geq 37.5^{\circ}\text{C}$  plus any parasitemia or axillary temperature  $\geq 37.5^{\circ}\text{C}$  plus *P. falciparum*  $> 5000/\mu\text{L}$ .

#### 11.3.1.2 Incidence of first or only *P. vivax* infection

The analyses approach to this objective is identical to the one for incidence of 1st or only *P. falciparum* episode. Analyses will include incidence of 1st or only episode detectable by PCR or light microscopy as well as infections exceeding different density cut-offs.

#### 11.3.1.3 Time-to-first *P. vivax* infection

Time to first infection will be analyzed using standard survival analysis, including log rank test for the comparison of survival curves and cox regression for modeling survival times. Time at risk will be defined as as outlined above. Cox regression analyses will be adjusted for possible covariates include infection status at baseline (i.e. before start of treatment), sex, age, host genetic traits, and nutritional state of child. Analysis will include analyses of time to 1st *P. vivax* only infection detectable by PCR or light microscopy as well as infections exceeding different density cut-offs.

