### **6.1.6 Active Surveillance**

Following the collection of the 10 mL venous blood sample the study team will contact each participating child every 2 weeks and conduct a brief clinical evaluation of each child during a clinic held at the participant's school.

The study team will specifically perform the following tasks:

- Record axillary body temperature of the child,
- Assess the child for symptoms of malaria infection,
- Determine if the child is suffering from symptomatic malaria (or clinical signs and symptoms of anemia),
- Check the fingers of the child for redness or signs of irritation from lancet finger punctures.
- Record information relating to:
  - history of bed net use for the study participant since the previous visit,
  - participant's history of illness since previous visit,
  - history of malaria treatment for the study participant since previous visit,
- Check the child's health records booklet for recent health center visits and record applicable information,
- Inform the child's teacher and school administration of the next follow-up visit and the reasons for the tasks to be performed.

If the participant is judged to be suffering from malaria illness at the time of the morbidity surveillance visit, finger prick blood samples will be collected for determination of parasitaemia and Hb levels. The presence of malarial parasites will be diagnosed in the field using RDT. For children excluded from undertaking RDT tests, blood smears will be read overnight for malaria diagnosis. Upon positive RDT or positive blood smear or in the case of moderate-to-severe anemia (Hb <8.0 g/dL) the study team will initiate treatment as per national standard treatment guidelines.

In the first 12 weeks of follow-up, a 250 µL finger prick blood sample will be collected at 2 weekly morbidity surveillance visits. Thereafter a finger prick sample will be collected every 4 weeks only.

The blood samples will be used to produce blood smears for assessing blood-stage malaria infection, type of *Plasmodium* parasite(s), and level of parasitaemia. A portion of this sample will be collected in a microtainer for further analysis (i.e., PCR/LDR-based diagnosis of malaria infection and for immunological studies). A few drops of blood will be collected on a filter paper for detection of gametocytes.

In total the team will conduct 16 follow-up visits that will include 11 finger prick blood sampling time points.

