All enrollment, baseline and active follow-up visits will be done by 2 mobile teams in the study communities. A 3rd team will help during the intensive DOT pre-treatment phase of the study. Each school will be visited on the same days over a 2-week period. Symptomatic children detected during the study clinics will be referred to the Albinama health centre or Maprik Hospital.

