**Follow-up and Morbidity Surveillance**

Finger prick blood samples of approximately 200 -250 µL will be collected every two weeks for the first 12 weeks and 4 weekly thereafter from each child participating in the study. Additional samples will be taken from symptomatic individuals at both active and passive morbidity surveillance visits. Blood samples will be obtained by the finger-stick method. This sample will provide adequate blood for the preparation of thin/thick blood smears to detect the presence of malaria parasites, type of malaria parasites, and level of parasitaemia. At baseline and the final visit, part of the sample will also be used to determine Hb concentration. The samples collected in microtainers will be processed into cell pellet (for DNA preparation, PCR/LDR-based diagnosis of malaria parasites and Duffy genotyping) and plasma (for immunological investigations).

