#### **11.1.2.3 Time to first *P. falciparum* / *P. vivax* infection**

For the analyses of time to first *P. falciparum* / *P. vivax* infection children will be at risk until they either experience a *P. falciparum* / *P. vivax* infection or they are treated with antimalarial drug for another malarial infection. At the time of the first antimalarial treatment, the child will be censored from analysis.

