### 11.3.2 Secondary Outcome Measures

Analyses for secondary *P. falciparum*, *P. vivax*, *P. malariae* and *P. ovale* outcomes follow identical approaches as those outlined above for *P. vivax* infections and *P. falciparum* morbidity.

Statistical analyses will be done using STATA, SAS and BUGS statistical software.

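### Time to first P. vivax infection is largely grouped at 11 sampling dates; the planned Cox model should name a tie or grouped-time method, since Breslow ties would shrink the hazard ratio modestly

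*Protocol*

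**What the plan says.** Section 11.3.1.3 of the protocol fixes the method: "Time to first infection will be analyzed using standard survival analysis, including log rank test for the comparison of survival curves and cox regression". Covariate adjustment follows, and the analysis is done for PCR-detected and microscopy-detected infections. Neither ties nor interval censoring is mentioned. Section 11.3.2 names the programs, with no options: "Statistical analyses will be done using STATA, SAS and BUGS statistical software".

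The sampling plan is in section 4. Routine samples are two weeks apart up to week 12 and four weeks apart from then on, and the section lists the dates: "i.e. weeks 2, 4, 6, 8, 10, 12, 16, 20, 24, 28 and 32". Section 6.1.6 gives the count, "In total the team will conduct 16 follow-up visits that will include 11 finger prick blood sampling time points", and adds on the calendar: "Each school will be visited on the same days over a 2-week period".

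Sampling is not confined to that grid. Section 6.2.2.1, under follow-up and morbidity surveillance, says: "Additional samples will be taken from symptomatic individuals at both active and passive morbidity surveillance visits".

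On censoring for this endpoint, section 11.1.2.3 says: "At the time of the first antimalarial treatment, the child will be censored from analysis".

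**The concern.** The exact onset of a blood-stage infection is not observed. A child negative at week 12 and positive at week 16 was infected somewhere in those four weeks. Because both arms share one calendar and few distinct dates, many children become positive at the same recorded time.

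Cox regression needs a rule for such ties. Under the Breslow approximation every tied child stays in the full risk set, and the estimate drifts toward a ratio of interval risks, which lies closer to 1 than the ratio of hazards. An identical schedule in both arms does not prevent this.

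The contribution of long-lasting liver stages to P. vivax infection is the first primary objective, and the hazard ratio is one of the figures that will express it. A shrunken ratio understates that contribution, even though the error is on the cautious side for testing.

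**Working it through.** **Inputs.** From section 11.2.1: median time to re-infection 54 days (PCR) and 118 days (light microscopy, LM) in the Madang study; design hazard ratios 0.70 (PCR) and 0.66 (LM); 200 per arm; 90% power; and a 50% decrease in time to infection after bednet distribution. Halving is what is written, while bednets might be expected to lengthen the time, so the medians are taken halved, unchanged and doubled. Follow-up is 32 weeks = 224 days. Alpha is not stated; 0.05 two-sided is assumed.

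**The plan's own figure.** Schoenfeld events = 4(1.960 + 1.282)²/(ln HR)². This gives 331 for HR 0.70 and 244 for HR 0.66. Dividing by the exponential event probability over 224 days, averaged over the arms with the median on the control arm, gives per arm:

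- PCR: 168, 183 and 237 (medians 27, 54 and 108 days)
- LM: 140, 186 and 293 (medians 59, 118 and 236 days)

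No single reading gives 200 for both. That is a separate matter; 200 per arm is used below as the number of evaluable children.

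**Why Breslow shrinks the ratio.** For one sampling date, with d₀ and d₁ events among n₀ and n₁ at risk, the Breslow score equation d₁ = (d₀ + d₁)·n₁θ/(n₀ + n₁θ) solves to θ = (d₁/n₁)/(d₀/n₀), the ratio of interval risks. With exponential onset at rate λ and interval length h, this is

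(1 − exp(−0.70λh)) / (1 − exp(−λh)).

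For a 54-day control median, λ = ln 2/54 = 0.01284 per day:

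- h = 14 days: 0.1182/0.1645 = 0.719
- h = 28 days: 0.2224/0.3019 = 0.737

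The complementary log-log link undoes this exactly: for h = 14, ln(1 − 0.1182)/ln(1 − 0.1645) = 0.70.

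**All 11 dates together.** Expected counts at weeks 2 to 12 and 16 to 32 were put into the Breslow and Efron score equations (large-sample limits, no simulation noise). Events per date are for 200 per arm without loss.

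| Assay, true HR | Control median (days) | Events per date | Breslow | Efron |
|---|---|---|---|---|
| PCR, 0.70 | 27 | 36 | 0.742 | 0.703 |
| PCR, 0.70 | 54 | 33 | 0.725 | 0.701 |
| PCR, 0.70 | 108 | 25 | 0.714 | 0.700 |
| LM, 0.66 | 59 | 32 | 0.685 | 0.661 |
| LM, 0.66 | 118 | 24 | 0.674 | 0.660 |
| LM, 0.66 | 236 | 15 | 0.667 | 0.660 |

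The shift under Breslow is 0.014 to 0.042 (PCR) and 0.007 to 0.025 (LM). With a front-loaded hazard (Weibull shape 0.6) the PCR shift is 0.012 to 0.031.

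**Power at 200 per arm** (600 simulated trials per row, same 11 dates, no loss):

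| Assay, median (days) | Breslow Cox | Efron Cox | Log-rank | Cox on true times |
|---|---|---|---|---|
| PCR, 27 | 0.882 | 0.923 | 0.923 | 0.927 |
| PCR, 54 | 0.873 | 0.908 | 0.905 | 0.900 |
| PCR, 108 | 0.810 | 0.832 | 0.835 | 0.832 |
| LM, 59 | 0.950 | 0.968 | 0.968 | 0.970 |
| LM, 118 | 0.905 | 0.923 | 0.923 | 0.922 |
| LM, 236 | 0.742 | 0.753 | 0.752 | 0.752 |

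The grouped-time model stayed within 0.01 of the true ratio, with power within 0.005 of Efron in every row.

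**Null.** With HR = 1 (medians 27 and 54 days) all methods averaged 0.998 to 1.007. Log-rank rejected in 0.055 and 0.068 of trials, against 0.052 and 0.063 for Cox on the true times.

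**The case against.** Four objections have weight.

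First, the protocol names no tie method and does not say that a detection date counts as the exact onset. Cox with Efron ties is also standard Cox regression. A reader might infer that planned Cox regression is biased as such, or that the listed programs will apply Breslow. The documents support neither: section 11.3.2 lists software without options, and the attenuation belongs to one approximation. This stands, and is why the point is conditional. A tie option is also commonly left to a statistical analysis plan. What remains is that the protocol itself sets the sampling grid and names the model, without fitting one to the other.

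Second, a reader might infer that infection can be seen only at the 11 scheduled samples. That is too strong. Symptomatic children give further samples at active visits and at the health centre, and those dates break ties. The calculation contains none, so it leans toward the larger effect.

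Third, the effect is small. At a 54-day median, ln(0.725/0.70) = 0.035, against a standard error of about 2/√331 = 0.110, so about a third of one standard error. It is absent under no effect, and the planned log-rank test keeps its power. It would be wrong to conclude that the trial is underpowered because of ties. Section 11.2.1 raises the 200 per arm to allow for losses, and section 4 enrols 250 to 300 per arm.

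Fourth, section 8.1.1 lists several primary outcomes over two species and two assays, and first infections are also analysed as incidence by Poisson regression. There is no single primary hazard ratio; the point concerns the P. vivax hazard ratios from Cox regression.

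**Conclusion.** The point holds as a minor one. Most first P. vivax infections will be recorded on a coarse shared grid, ties will be heavy, and section 11.3.1.3 does not provide for them. If Breslow ties are used, the hazard ratio is pulled toward 1 by at most about 0.04 and the Cox test loses about 1 to 5 points of power at 200 evaluable children per arm. There is no bias under no effect, and the log-rank comparison is sound as planned.

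These sizes assume exponential onset, perfect detection, samples exactly on schedule, no off-schedule samples and no censoring at treatment. Spread in visit days or sampling of symptomatic children would make the bias smaller. Losses hardly change it: with 262 per arm and 25% dropout, Breslow gives 0.726 for a true 0.70 (54-day median) and 0.673 for a true 0.66 (118-day median), while Efron gives 0.703 and 0.660.

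**What to change.** In section 11.3.1.3, specify Cox regression with Efron handling of ties. A grouped-time proportional-hazards model does equally well: complementary log-log link, one baseline term per sampling interval, and off-schedule detections assigned to the interval in which they fall. Keep the log-rank test for comparing the curves.

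The cost is one sentence. No data, visits or sample size change, and the result is still a hazard ratio with the same interpretation.
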